#### Outcome variables of projects A1 and A2

Primary outcome variable for both A1 and A2 projects will be the Action Research Arm test score (ARAT). Secondary outcome variables are the scores of: Motricity Index (MI) of arm and leg, Fugl-Meyer for the arm (FM-arm), Erasmus modification of the Nottingham Sensory Assessment (EmNSA), Letter Cancellation Task (LCT), Nine Hole Peg test (NHPT), a structured participant interview of real arm use using the Motor Activity Log (MAL), Stroke Impact Scale (SIS version 3.0) and Nottingham Extended ADL (NEADL). With the exception of the NEADL and SIS, all assessments will be applied to all 180 patients weekly in the first 5 weeks post stroke. Subsequently, follow-up assessments will be made at 8, 12 and 26 weeks after stroke.

The ARAT test is a performance test which assesses the ability to perform gross movements and the ability to grasp, move and release objects differing in size, weight and shape [41]. The original test consists of 19 items, rated on 4-point ordinal scales (0 to 3). By removing 4 items, a hierarchical 1-dimensional scale has been constructed [42]. The ARA test has been shown to be valid, reliable and responsive [35]. The minimal clinically important difference (MCID) will be set at about 10% of the range of the scale, i.e. 6 points [15]. For project A2, return of dexterity will be defined as 10 points or more on the ARAT [5].

The Motricity index (MI) reliably and validly assesses the presence of paresis in stroke patients by testing 6 functions rated from 0 to 100 points for each limb [8,43].

The FM-arm score is a reliable and valid motor performance test [44,45] and evaluates the ability to make movements outside the synergistic pattern.

A translated and adapted version of the MAL will be used [46] which contains the 14 original activities, 11 additional activities, and 1 optional activity chosen by the patient. Reliability and validity of the MAL has been proved in a number of studies [46]. The MAL will be administered to each applicant and, if available, their caregivers. It will be used to independently rate how well (11-point Quality of Movement [QOM] scale) and how much (11-point amount-of-use [AOU] scale) the paretic arm was used spontaneously to accomplish 30 activities of daily living outside the laboratory [47].

The EmNSA is a 3 point ordinal scale measuring sharp-blunt discrimination, two-point discrimination and proprioception. With exception of the two-point discrimination, intra- and inter rater reliability are good to excellent (Kappa: 0.58 to 1.00, [48]).

The Nine Hole Peg Test (NHPT) is a reliable and valid test that measures manual dexterity [49,50] by measuring the speed with which a patient grasps and inserts (and removes) 9 pegs into a grid of vertical holes. The test will be discontinued after 150 seconds if the patient is still unable to insert any pegs. Reliability and validity have been assessed and norms are available [49,50].

Visual inattention will be evaluated by the letter cancellation test which has shown high test-retest reliability, ranging from 0.78 to 0.90 (p < 0.001) for the number of omissions on the sound and neglected field sides respectively [8].

The arm-hand domain of the Stroke Impact Scale (SIS, version 3.0) will be used to evaluate patients' perceived outcome for the paretic upper limb. Version 3.0 of the SIS is a full-spectrum health status interview that measures changes in 8 impairments, function and quality of life subdomains following stroke [51]. Each domain will be analysed separately. The upper limb part of the SIS includes 5 questions about patients' perceived competency to keep their balance, to transfer, to walk in the house and negotiate stairs, to get in and out of a car and to move about in their own community. Each item is scored from 'not difficult at all' to 'cannot do at all' on a 5-point rating scale. A difference of 5 points (10%) on the 'hand function' domain of the SIS is perceived as clinically relevant [17]. The SIS has shown excellent clinimetric properties in terms of concurrent and construct validity, test-retest reliability and responsiveness [52,53].

The Nottingham Extended ADL scale is based on a self-report questionnaire about levels of activity actually performed [54]. The scale has proved to have reasonable hierarchical (ordinal) properties in stroke patients [55].

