**Methods/design:**

180 participants suffering from an acute, first-ever ischemic stroke will be recruited. Functional prognosis at the end of the first week post stroke is used to stratify patient into a poor prognosis group for upper limb recovery (N = 120, A2 project) and a group with a favourable prognosis (N = 60, A1 project). Both groups will be randomized to an experimental arm receiving respectively modified CIMT (favourable prognosis) or EMG-NMS (poor prognosis) for 3 weeks or to a control arm receiving usual care. Primary outcome variable will be the Action Research Arm Test (ARAT), assessed at 1,2,3,4,5, 8, 12 and 26 weeks post stroke. To study the impact of modified CIMT or EMG-NMS on stroke recovery mechanisms i.e. neuroplasticity, compensatory movements and upper limb neuromechanics, 60 patients randomly selected from projects A1 and A2 will undergo TMS, kinematical and haptic robotic measurements within a repeated measurement design. Additionally, 30 patients from the A1 project will undergo fMRI at baseline, 5 and 26 weeks post stroke.

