(1) Is an early modified CIMT programme more effective in terms of recovery of the paretic upper limb than conventional care in stroke patients with a favourable prognosis for recovery of the upper limb? (Project A1)

(2) Is an early EMG-NMS programme for wrist and finger extensors more effective in terms of return of dexterity than conventional care in patients with initially poor prognosis for upper limb recovery? (Project A2)

(3) Are modified CIMT-induced gains reinforced by recruitment of cortical activation in the ipsilesional hemisphere when compared to usual care? (Project B1)

(4) Can improved performance of a functional reaching task be explained on the basis of behavioural compensation strategies? (Project B2)

(5) How and to what extent do wrist neuromechanical properties, i.e. stiffness, motor function and control change in the first 6 months post stroke? (Project B3)

(6) Does early intervention affect endpoint neuromechanics (Project B3)

(7) How are improvements in dexterity longitudinally related to changes observed in kinematics, neuromechanics and cortical activation (Project C).

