### Project A2

#### Background and hypotheses

Patients with a poor prognosis for functional recovery (estimated to include about 2/3 of all stroke patients with a MCA stroke) will undergo an intensive stimulation programme of wrist and finger extensors using EMG-triggered neuromuscular stimulation (EMG-NMS). These patients are unable to move their paretic upper limb voluntarily. Return of voluntary motor control can so far only be facilitated by somatosensory input and imaginary movement. The assumed positive impact of EMG-NMS is based on the finding that 2 hours of sensory stimulation of the median nerve of a paretic limb may result in improved pinch strength [23]. This improvement in muscle strength correlates with the stimulus intensity and has been identified in the absence of motor training. Virtual imaging has also been found to improve cortical plasticity and motor performance of the upper limb in chronic stroke [24]. The above results suggest that somatosensory stimulation, combined with virtual imaging by applying EMG-NMS, may be a promising adjuvant therapy to initiate active motor control in stroke patients with an upper limb deficit. It is hypothesized that cortical ipsi-lesional and contra-lesional plasticity is facilitated by EMG-NMS of wrist and finger extensors especially early after stroke, when the outcome in terms of dexterity has not yet been defined, hence increasing the probability of return of some functional dexterity [24]. In addition, it is believed that the movement imagery component causes neural networks in the motor cortex, associated with the specific imagined movement, to be stimulated and reinforced. Evidence supporting this theory has been found using fMRI [24]. Based on this 'use it or lose it' principle [36-38], one may assume that a higher percentage of patients in the experimental group will regain some dexterity in terms of ARAT scores, i.e. > 9 points [5], when compared to the control group. If triggering with the paretic limb proves to be not possible, EMG activity of the non-paretic wrist and fingers extensors will be used to trigger activation of the paretic limb, since ipsilateral activation is also known to reinforce cortical activity in the affected hemisphere after stroke [39].

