#### Power analysis for project A2

Based on a previous cohort study with 101 first-ever MCA strokes [8], patients with a poor prognosis have a probability of about 6% to regain some dexterity (ARAT > 9 points) at 6 months post stroke [8]. In project A2 we assume a proportional difference of 12% in favour of the experimental group. Based on a statistical power of 80% with an alpha of 5% and a test-retest reliability of 0.9 for ARAT with 5 repeated measurements, 120 patients should be enough to show statistical significance in favour of EMG-NMS in the poor prognosis group.

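### Project A2 names the ARAT score as its primary outcome but is sized on the proportion reaching ARAT 10 or more at 6 months, so the stated power does not belong to the named primary

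*Protocol article*

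**What the plan says.** Two places assign primary status. The outcome section covers both trials in one sentence: "Primary outcome variable for both A1 and A2 projects will be the Action Research Arm test score (ARAT"). The Methods/design part of the abstract says: "Primary outcome variable will be the Action Research Arm Test (ARAT), assessed at 1,2,3,4,5, 8, 12 and 26 weeks post stroke". Neither mentions a cut-off, and neither picks out one visit.

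Four places describe A2 as a comparison of proportions or set up such a comparison:
- The research question in the Background asks whether early EMG-NMS is "more effective in terms of return of dexterity than conventional care in patients with initially poor prognosis for upper limb recovery".
- The A2 hypothesis expects that "a higher percentage of patients in the experimental group will regain some dexterity in terms of ARAT scores, i.e. > 9 points".
- The A2 power analysis starts from the premise that "patients with a poor prognosis have a probability of about 6% to regain some dexterity (ARAT > 9 points) at 6 months post stroke" and continues: "In project A2 we assume a proportional difference of 12% in favour of the experimental group".
- The outcome section adds, in its description of the ARAT: "For project A2, return of dexterity will be defined as 10 points or more on the ARAT".

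The last sentence is a definition. It does not say that the dichotomy takes the place of the score, and the dichotomy is not in the list of secondary outcomes. The A2 power analysis also invokes a test-retest reliability of 0.9 with 5 repeated measurements, as the A1 power analysis does for the score.

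**The concern.** The power statement should describe the test of the primary outcome. For A2 it describes a test of a proportion at one visit, while the named primary is a score measured at eight visits. No A2 power statement is given for a difference in score.

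Two things are at stake. First, a reader cannot tell what power A2 has for its primary comparison. Second, a comparison of scores and a comparison of proportions could each be reported as the primary result with support from the text. They are different tests on a population in which most patients are expected to stay below 10 points, and they can disagree.

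**Working it through.** **Inputs from the protocol article.** Control rate 6% at 6 months; difference 12%, read as 12 percentage points (6% versus 18%); 80% power; alpha 5%, sidedness not stated; 120 patients, taken as 60 per arm. On the integer ARAT score, above 9 and 10 or more are the same cut-off. The clinically important difference on the score is 6 points. The only SD given is 8 points, in the A1 power analysis.

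**1. The plan's own figure.** For two proportions with pooled variance under the null, and mean rate p̄ = 0.12:

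n per arm = [z(1−α/2)·√(2p̄(1−p̄)) + z(1−β)·√(p1(1−p1)+p2(1−p2))]² / (p2−p1)²

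= [1.96·√0.2112 + 0.8416·√0.2040]² / 0.0144 = (0.9007 + 0.3801)² / 0.0144 = 113.9, so 114 per arm and 228 in total. One-sided, the total is 180. The stated 120 is not reproduced. Reading the 12% as the experimental rate (6% versus 12%) moves further away: 712 two-sided, 562 one-sided.

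The reliability term does not bridge the gap. Averaging five measurements with correlation 0.9 multiplies the variance by (1 + 4×0.9)/5 = 0.92, which gives 228 × 0.92 ≈ 210 two-sided or 180 × 0.92 ≈ 166 one-sided. Multiplying by 0.9² = 0.81 gives about 185 two-sided or 146 one-sided. A factor of 1 − 0.81 = 0.19 gives about 43 two-sided. None of these gives 120, and none applies to a single proportion at one visit.

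**2. Power of the proportion test at 60 per arm.**

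Two-sided: Φ[(0.12·√60 − 1.96·√0.2112)/√0.2040] = Φ[(0.9295 − 0.9007)/0.4517] = Φ(0.064) ≈ 53%.

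One-sided, with 1.645 in place of 1.96: Φ[(0.9295 − 0.7559)/0.4517] = Φ(0.384) ≈ 65%.

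**3. Power of a score test at 60 per arm, if the effect is a 6-point shift in mean.** Power = Φ[6/(SD·√(2/60)) − 1.96]. The A2 SD is not given, so a range is shown.

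| Assumed SD | Power |
|---|---|
| 8 (the A1 value) | 98% |
| 10 | 91% |
| 12 | 78% |
| 15 | 59% |

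**4. Both tests on the same simulated data.** There were 3,000 to 4,000 trials per scenario, with 60 per arm. Assumptions, none from the document: responders are uniform on 10–57; a set share of non-responders score 0 and the rest are spread over 0–9. Rates are 6% versus 18%, and all tests are two-sided.

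| Scenario | Proportion test | Test on score | Disagree |
|---|---|---|---|
| 20–80% of non-responders at 0, rank test | 53–54% | 20–30% | 31–41% |
| 90% at 0, rank test | 53% | 37–38% | 25% |
| 20–90% at 0, t test | 53% | 42–46% | 15–19% |
| 50% at 0, treated non-responders also gain 0–2 points (capped at 9), rank test | about 53% | 90–91% | about 40% |

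**5. No effect (6% or 12% in both arms).** Each test alone rejects in about 4–6% of trials. Taking whichever of the two is significant rejects in about 7% (proportion or t test) to 8–9% (proportion or rank test). Two independent tests would give 1 − 0.95² = 9.75%; the two ARAT tests are correlated.

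**The case against.** The strongest reply is that A2 points one way. Its question, hypothesis and sample size are all about return of dexterity, the Discussion restates the A2 hypothesis in those terms, and the outcome section supplies a cut-off for A2 only. On that reading the ARAT is one instrument, used as a score in A1 and as a cut-off in A2, and what is missing is a linking sentence. Much of this stands: the dichotomy is probably what was intended. But the one sentence that ranks outcomes for A2 says score, and the reliability term in the A2 power analysis fits a repeated score better than a single proportion.

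A second reply is that the choice of test belongs in a statistical analysis plan, which is not shown. That holds for the test itself: neither a rank test nor a z test appears in the article. It does not hold for which variable is primary, where statements within this document do not agree.

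A reader might also infer that the proportion is clearly the more powerful choice. The document does not support this. The ordering depends on assumed score distributions, and it reverses if non-responders also gain a little.

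Nor does the document show that the false-positive rate is already inflated. The 7–9% applies only if the choice is made after seeing the data, which an analysis plan may rule out.

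**Conclusion.** The point holds as a conflict between the named A2 primary outcome and the outcome on which A2 was sized. The stated 80% power is not power for the ARAT score, and the text gives the dichotomy no rank. The intent can largely be inferred, so this calls for clarification and does not show a flawed design.

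The firm figure is about 53% two-sided power (65% one-sided) for the proportion at 6% versus 18%, assuming equal arms of 60, no dropout, and the 12% read as percentage points. The range of about 20% to over 90% for a score test rests on assumed distributions. It shows only that the choice can matter a great deal, not which test does better. The 7–9% false-positive rate is conditional on a choice made after seeing the data.

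**What to change.** In the abstract and in the section on outcome variables of projects A1 and A2, state that the A2 primary outcome is the proportion of patients with ARAT 10 or more at 26 weeks, with the ARAT score and all other visits secondary. Keep the score as the primary outcome of A1.

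In the power analysis for project A2, remove the term for reliability of 0.9 with 5 repeated measurements, which does not apply to a single proportion. Restate the power for 120 patients at 6% versus 18%, with the sidedness given: about 53% two-sided or 65% one-sided.

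The cost is a few sentences and no new data. The downside is that the stated power becomes less favourable: naming the proportion as primary makes the shortfall against 80% explicit. The two-sided requirement for 80% would be 228 patients.

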#### The B projects of Explicit

The effect of modified CIMT on the process of neurological recovery is not fully understood. So far, it is assumed that the impairment of hand function is worsened by learned non-use and that this leads to a loss of cortical representation of the upper limb [37]. It is claimed that these processes can be reversed by constraining the unaffected limb, combined with intensive practice i.e. shaping of the paretic hand. However, the theory of learned non-use has been called into question and there is uncertainty about the nature of the improvements induced by modified CIMT, although some evidence exists that modified CIMT increases spontaneous use of the hand by recovery of existing deficits, either through reduction of learned non-use or by overcoming the sense of effort during movement [37]. In order to improve our understanding of mechanisms that may underlie functional recovery and therapy-induced effects our second objective will be to investigate the CIMT-induced plastic changes in the affected and non-affected hemispheres by fMRI and TMS and compare these with a control group (Project B1). To this end, 30 patients will be selected from project A1 viz. 15 from the experimental and 15 from the control group.

Although it is assumed that modified CIMT can improve dexterity in the acute or subacute phase, no studies have so far analysed in detail whether this improvement reflects reduction of basic motor impairments or works by learning compensatory movement strategies (project B2). Finally, understanding the observed adaptive behavioural movement strategies requires that the neuromechanical changes of the musculoskeletal system are assessed. For this purpose, it is of vital importance to understand the relationship between parameters characterizing CNS function (such as TMS and fMRI) and parameters describing end-point neuromechanical behaviour (project B3).

#### Recruitment for the B projects

For the B projects 30 subjects from project A1 with an initially favourable prognosis within the first week post stroke will be recruited to undergo fMRI, TMS, kinematical measurements and haptic robotics. As a control group, 30 patients with an initially poor prognosis (i.e. from project A2) will be recruited for TMS (project B1) and haptic robotics.

#### Power analysis

Concerning fMRI, calculation is based on measures of Brodmann areas 9 and 46 in which the fMRI activation is assumed to be more difficult than in primary motor and sensory cortices, thus, a conservative estimate is obtained. The mean increment of the intensity of the signal in the volumes of interest (VOI 's, %) and the standard deviation of the normal signal intensity have both been found to be 1.5, whereas the normalized minimal difference between groups that is detectable with fMRI is estimated to be 1.15. Calculation of the required sample size is based on the formula {N = [2*(z(1-α/2)-z(1-β)) raise to square*(var(n)/Δ)] in which α and β are set at 0.01 and 0.10, respectively. This leads to a sample size of 13 patients in both the control and experimental groups. Based on an expected drop-out rate of 10%, we would need at least 30 stroke victims. It has been calculated that this number will also guarantee sufficient power for projects B2 and B3

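### The fMRI sample size of 13 per group does not follow from its stated inputs, which require 23 per group; 13 gives about 56–64% power, not 90%

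*Protocol article*

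**What the plan says.** The power analysis for the B projects (Protocol article, section "Power analysis" under the B projects) gives all its inputs. On the mean signal increment and its spread it says that the increment and "the standard deviation of the normal signal intensity have both been found to be 1.5". On the effect it says that "the normalized minimal difference between groups that is detectable with fMRI is estimated to be 1.15". The formula is printed as "N = [2*(z(1-α/2)-z(1-β)) raise to square*(var(n)/Δ", with the error rates given as "in which α and β are set at 0.01 and 0.10, respectively". The result is: "This leads to a sample size of 13 patients in both the control and experimental groups".

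Attrition is then added: "Based on an expected drop-out rate of 10%, we would need at least 30 stroke victims". The introduction to the B projects splits the 30 patients from project A1 as "15 from the experimental and 15 from the control group". The power section ends: "It has been calculated that this number will also guarantee sufficient power for projects B2 and B3".

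**The concern.** The formula, the inputs and the result are all printed, so they can be checked against one another, and they disagree. The printed formula departs from the standard two-group formula in two places: it subtracts z(1-β) where it should add it, and it divides by Δ where it should divide by Δ squared. Restoring the standard form does not rescue the result, because the corrected number is well above 13.

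At stake is how the B1 arm comparison will be read. Research question 3 asks whether gains from modified CIMT go with ipsilesional recruitment when compared with usual care, and the fMRI contrast of 15 against 15 is the test of that. A null result would be presented as coming from a test with 90% power when the design has much less at the stated alpha.

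**Working it through.** **Inputs, all from the B-project power analysis.** Two-sided alpha 0.01 (the formula uses 1-α/2), so z = 2.576. Beta 0.10, so z = 1.282. Difference Δ = 1.15, called normalized. SD 1.5. Stated result 13 per group. Dropout 10%.

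**Step 1: the formula as printed.** (2.576 − 1.282)² = 1.675.
- Variance 1: 2 × 1.675 / 1.15 = 2.9.
- Variance 1.5² = 2.25: 2 × 1.675 × 2.25 / 1.15 = 6.6.

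Neither is 13.

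**Step 2: the standard formula,** N per group = 2 × (z(1-α/2) + z(1-β))² × var / Δ². Here (2.576 + 1.282)² = 14.88 and Δ² = 1.3225.
- Δ standardized, variance 1: 2 × 14.88 / 1.3225 = 22.5, so 23 per group (25 by noncentral t).
- Δ in signal units, variance 2.25: 2 × 14.88 × 2.25 / 1.3225 = 50.6, so 51 per group (53 by noncentral t).

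A one-sided alpha of 0.01, which the formula does not use, would still need 20 per group (22 by t).

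**Step 3: can 13 be reproduced?** Two routes come close, and neither is a valid calculation from the stated inputs.
- Plus sign, variance 1, Δ unsquared: 2 × 14.88 / 1.15 = 25.9, and half of that is 12.9. This leaves Δ unsquared and halves a number that the leading factor 2 already makes per-group.
- The standard formula with 1.5 used as the standardized effect: 2 × 14.88 / 2.25 = 13.2, which rounds up to 14. The text gives 1.15 as the difference, and its mean increment divided by its SD is 1.5 / 1.5 = 1.0, not 1.5.

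**Step 4: the dropout step.** 13 / 0.9 = 14.4, so 15 per group and 30 in total. This step is consistent with the 13.

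**Step 5: power of the chosen size,** unadjusted two-group comparison, two-sided alpha 0.01.

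| Standardized difference | n per group | t-test (noncentral t) | Normal approximation |
|---|---|---|---|
| 1.15 | 13 | 56% | 64% |
| 1.15 | 15 | 65% | 72% |
| 1.15 / 1.5 = 0.767 | 13 | 23% | 27% |
| 1.15 / 1.5 = 0.767 | 15 | 27% | 32% |

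With 13 per group, 90% power at alpha 0.01 requires d of about 1.63 by t-test. By the normal approximation it is (2.576 + 1.282) × √(2/13) = 1.51.

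**The case against.** **The formula may be a printing accident.** It is flattened to text, with an unmatched brace and an exponent written in words, so a lost superscript or a wrong sign is plausible. That stands, and the misprint alone would be minor. It does not help the result, because the restored formula gives 23 rather than 13.

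**The power figures may be too low.** They assume an unadjusted comparison at one time point. The B1 design has three scans, and a baseline-adjusted analysis could do better. With 13 per group and d = 1.15, an assumed baseline correlation of 0.5 gives d = 1.15 / √(1 − 0.25) = 1.33 and about 72% power by t-test; an assumed 0.7 gives 1.15 / √(1 − 0.49) = 1.61 and about 89%. The article also calls its estimate conservative, because it is based on areas assumed harder to activate than the motor cortex. These points limit what can be said about the power finally achieved. They do not make 13 the outcome of the stated calculation, which contains no correlation term.

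**The raw-unit reading goes against the text's own word.** The article says normalized, so d = 1.15 is the main reading. The 0.767 figures belong in the range only because the SD of 1.5 is quoted alongside and the formula's variance is not defined.

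**Stronger readings are not supported.**
- A reader might infer that 13 can only have come from halving 25.9. Step 3 shows a second route that comes close, so the origin stays open.
- A reader might infer that the claim for B2 and B3 is false. The article says that the adequacy was calculated, and a condensed article may leave out that working, so its absence is not an error.
- A reader might infer that the whole mechanistic programme falls with this number. B3 uses 60 patients, 30 from each prognosis group, and project C is a longitudinal association model rather than a two-arm test. The calculation directly governs only the B1 fMRI arm contrast.

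**Conclusion.** The point holds for the B1 fMRI comparison. At the stated alpha and power, the stated difference needs 23 per group (25 by t-test), or 51 (53) if 1.15 is in signal units. At d = 1.15 the stated 13 has about 56% to 64% power, so the chance of missing the target difference is about 36% to 44% rather than the stated 10%. Full retention of 15 per group narrows this gap but does not close it. These figures rest on a two-sided alpha of 0.01, equal groups, a common variance and no baseline adjustment. The A1 and A2 primary ARAT comparisons have their own sample-size calculations and are untouched.

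**What to change.** 1. Print the formula as N per group = 2 × (z(1-α/2) + z(1-β))² × var / Δ².
2. State whether Δ = 1.15 is standardized or in signal units, and which variance is used with it.
3. Keep 15 + 15. Replace the implied 90% power with the power that this size has at alpha 0.01: about 56–64% at d = 1.15 with 13 evaluable per group, if Δ is confirmed as standardized. Equivalently, state the difference detectable with 90% power, d of about 1.63 by t-test. If a baseline-adjusted analysis is the intended basis, state the assumed correlation and recompute.
4. Recheck the sentence on B2 and B3 if it relied on this calculation. If it rests on separate calculations, it can stand with a reference to them.

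Moving to alpha 0.05, at which 13 per group would have about 80% power by t-test at d = 1.15, would be a change of design rather than a correction, and is not needed here.

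The cost is a less favourable stated power. No extra patients or scans are required.
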